### Statistical Considerations

#### Blinding to Outcome Measures

The members of the Trial Steering Committee (TSC), the DMEC, and the trial statistician will be blinded to treatment allocation. The trial manager (TM) and physiotherapists will not be blind to allocation, as they will inform participants of their allocation and deliver the intervention. To further minimize observer bias, outcomes will be self-rated by the participant, and outcome assessments will be coordinated by the TM. The trial statistician will be masked to treatment group until after the main analysis is completed.

#### Sample Size

Our original sample size was based upon the SF-36 PF as our primary outcome; however, the significance level was reduced to 2.5% to accommodate 2 primary outcomes [31]. A large previous trial of CFS/ME using the SF-36 PF (the PACE trial) indicated a baseline mean score of 37 (SD 15) and an outcome score of 48 (SD 21) following 12 weeks of practitioner-led GET, an 11-point increase [11]. Based on these previous findings, and our estimate that GES will be less effective than GET, the sample size calculations are based on the assumption that a mean difference of 8 (SD 18) points between intervention arms at the 12-week follow-up will be a clinically useful difference on the SF-36 PF scale after 12 weeks [11]. Thus, assuming a significance level (alpha) of 2.5% and power of 80%, we require a minimum of 98 participants in each group. This sample size will be upwardly adjusted to allow for loss to follow-up and other compliance issues. Based upon previous trials, we expect about 10% loss to trial follow-up [17]; therefore, we will recruit 109 patients in each group (a total of 218).

Based on a previous trial of GET, in which the difference between baseline and 12 weeks was 5.4 points on the CFQ [11], we assume that a mean difference of 3 (SD 6) points will represent a clinically useful difference at the 12-week follow-up. Hence, assuming a significance level (alpha) of 2.5% and power of 80%, we require a total of 174 patients, which is less than the 218 to be recruited, so adequate power will be achieved.

#### Data Entry and Analysis

Data will be double entered by a dedicated data-entry researcher. The analysis and presentation of the trial will be in accordance with CONSORT guidelines including a flow diagram of enrollment, allocation, follow-up, and analysis [26,44]. We plan to use descriptive statistics to compare characteristics of invited individuals who did or did not agree to take part and eligible individuals who were randomized or not randomized (pending ethical approval). We will also examine differences between trial arms in important baseline participant characteristics.

#### Descriptive Statistics for Primary and Secondary Outcomes

Box plots will be used to assess the data distribution of continuous measures. Descriptive statistics will be broken down by intervention group at baseline and follow-up. Normality of the scales and regression residuals will be explored using diagnostic plots, and if the assumption of normality is violated, the data will be transformed. We will present means and standard deviations for all normally distributed measures, and medians and quartiles for nonnormal measures. Discrete outcomes will be described using both number and percentage.

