#### Missing Data

Item-level missing data on the primary and secondary outcome variables at baseline and follow-up will be imputed using mean replacement (prorating). Prorating will be implemented only when less than 20% of item responses per scale are missing. The reasons for missing baseline and follow-up whole-scale data will be summarized using the CONSORT diagram. We will identify baseline characteristics associated with missing data to allow us to impute data to do sensitivity analyses.

#### Analysis for Hypothesis 1

Our primary intention-to-treat analysis will compare the SF-36 PF and CFQ at 12 weeks between groups adjusted using multivariable linear regression analyses [45]. Intention-to-treat (ITT) analyses will be conducted on data from all randomized participants with information at follow-up (ie, modified ITT) regardless of any departure from the allocated treatment arm. We will adjust for our stratification factors (depression, center, and severity of disability) as well as baseline values of outcomes and treatment arm.

A secondary analysis will explore the association between treatment arm and having achieved a clinically useful improvement on the SF-36 PF (ie, an 8-point increase) and the CFQ (ie, a 3-point decrease) using chi-squared analysis.

Analysis of the secondary outcome, the CGI, will compare the proportions scoring “much” or “very much” better (1 and 2), the proportions scoring “a little better,” “no change,” or “a little worse” (3 to 5), and the proportions scoring “much” or “very much” worse (6 and 7) across treatment arms, using an ordinal logistic regression adjusting for our stratification variables.

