#### Sensitivity Analysis

Sensitivity analysis will be conducted to assess the impact of missing data on our results. We will estimate whole-scale missing data due to loss to follow-up using multiple imputation by chained equation. This will allow us to conduct a strict ITT for all respondents who took part at baseline. Following recent guidelines, we will also conduct a sensitivity analysis that will take into account the partially nested design of the study and, therefore, assess the potential impact of the “therapist effect” on our results [46]. Further analysis will be conducted to adjust for potential confounders, including sex and age.

A per-protocol analysis will serve as a further sensitivity analysis to investigate the robustness of the conclusions of the primary analysis, following departures from the randomized intervention policies. This will exclude those participants in the control arm who used a GET self-help approach. Subgroup analyses including only those meeting the Oxford or CDC criteria for CFS will also be undertaken. We will analyze moderators of improvement, such as these criteria, but also depression and severity of physical function and fatigue. These subgroup analyses are exploratory and will be interpreted with due caution [47].

#### Analysis for Hypotheses 2 and 3

Chi square will be used to describe any difference in satisfaction (ie, satisfied vs nonsatisfied) across treatment arms and any differences in SAEs, SARs, or serious deterioration (1+ vs none) across treatment arms.

The above plan is what we intend to do; however, the final analyses reported may differ from those planned, allowing for *post hoc* analysis where it is indicated [48]. We will report alternative methods if statistical models do not converge, and omit planned analyses that are superseded, redundant, or no longer of interest. We will report any changes in consequent papers.

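### Two standing permissions leave the reported primary result open: transforming outcomes that look non-normal takes the estimate off the 8- and 3-point scales, and planned primary, CGI or safety analyses may be omitted

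*Protocol article*

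**What the plan says.** **Transformation.** Under Descriptive Statistics for Primary and Secondary Outcomes, the authors plan to inspect plots both of the outcome scales and of the residuals from the regressions, and say that "if the assumption of normality is violated, the data will be transformed". The article names no transformation, no criterion for a violation and no effect measure for the transformed result.

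**Primary analysis.** Under Analysis for Hypothesis 1, the primary analysis will "compare the SF-36 PF and CFQ at 12 weeks between groups adjusted using multivariable linear regression analyses", with adjustment for baseline values and the stratification factors.

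**Target differences.** Under Sample Size, the differences regarded as clinically useful are 8 points (SD 18) on SF-36 PF and 3 points (SD 6) on CFQ, each at a 2.5% significance level and 80% power. The Discussion makes release of the booklet depend, among other things, on a clinically useful difference between the arms.

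**Departures from plan.** The closing paragraph of Analysis for Hypotheses 2 and 3 says that "the final analyses reported may differ from those planned", allows post hoc analysis, and lets the authors "omit planned analyses that are superseded, redundant, or no longer of interest". It ends: "We will report any changes in consequent papers".

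**Masking.** Under Blinding to Outcome Measures: "The trial statistician will be masked to treatment group until after the main analysis is completed".

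**The concern.** Both provisions are affirmative rules in the text. They are not details left for an analysis plan to supply.

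The transformation rule is worded as an instruction and covers regression residuals, so it cannot be set aside as purely descriptive. It also takes normality of the scales themselves as a trigger, although linear regression makes no assumption about the marginal distribution of the outcome. If it fires, the primary treatment effect is no longer in points, and the comparison on which the design and the Discussion rest cannot be made from the primary model.

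The omission clause applies to the plan as a whole and directly follows the safety comparison. Whether an analysis is still of interest can be judged after its result is known. Outcomes here are self-rated by participants who know their allocation, so a fixed list of analyses that will be reported whatever they show is a useful protection. The clause weakens it.

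**Working it through.** **1. The design is on the raw scale.** Inputs from Sample Size: difference 8, SD 18, alpha 2.5% (two-sided reproduces the figure), power 80%, loss 10%.

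- n per arm = 2 × (z for 1 − alpha/2 + z for power)² × (SD/difference)² = 2 × (2.241 + 0.842)² × (18/8)² = 2 × 9.505 × 5.0625 = 96.2, so 97. The noncentral-t version gives 98, the stated figure.
- 98/0.9 = 108.9, so 109 per arm and 218 in total, as stated.
- CFQ: 2 × 9.505 × (6/3)² = 76.0, so 77 per arm, or 78 with noncentral t. 78/0.9 = 86.7, so 87 per arm and 174 in total. The stated 174 is therefore reproduced with the 10% loss included.

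The stated sample sizes follow from raw-point differences, and none of them is wrong on this point. With 98 evaluable per arm, the normal approximation gives 80.8% power for 8 points and 89.6% for 3 points.

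**2. What a transformation does to those differences.** No transformation is named, so a log is used only for illustration.

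| Scale | Raw change | Ratio |
|---|---|---|
| SF-36 PF | 20 to 28 | 28/20 = 1.40 |
| SF-36 PF | 40 to 48 | 48/40 = 1.20 |
| SF-36 PF | 60 to 68 | 68/60 = 1.13 |
| SF-36 PF | 80 to 88 | 88/80 = 1.10 |
| CFQ | 30 to 27 | 27/30 = 0.90 |
| CFQ | 15 to 12 | 12/15 = 0.80 |

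A fixed point difference has no single value on the transformed scale, so a transformed coefficient cannot be set against 8 or 3.

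**3. Is a transformation needed to protect the error rate?** Null simulation with assumed inputs: 98 per arm; a right-skewed 0–100 score in steps of 5, mean 38, SD 21; baseline-adjusted linear regression; nominal 2.5%; 10,000 trials. The log was taken of the score plus 5.

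| Analysis | Rejection rate under no effect |
|---|---|
| Raw scores | 2.6% |
| Log scores | 2.4% |
| Scale chosen by residual skewness | 2.6% |
| Smaller of the raw and log p-values | 3.4% |

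The simulation standard error at 2.5% is √(0.025 × 0.975/10,000) = 0.16 percentage points. The first three rows agree with the nominal level. Only choosing by the result inflates it, and the article does not propose that.

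**4. Reach of the omission clause.** The clause refers to the plan above it. That plan contains the primary regressions and the CGI comparison (Analysis for Hypothesis 1) and the between-arm comparison of serious adverse events, serious adverse reactions and serious deterioration (Analysis for Hypotheses 2 and 3). No sentence exempts any of them.

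**The case against.** **A condensed article with a conventional fallback.** Transforming non-normal data is common, and an analysis plan may fix the details. That is fair as to which transformation and which criterion. It does not answer the point, because the article states the rule and the permission positively.

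**The scale is not wholly lost.** Transformation is conditional on a judged violation, the secondary responder analysis uses 8 and 3 raw points, and medians and quartiles are promised for non-normal measures. This stands: what would lose its units is the regression estimate. The responder analysis, however, is itself open to omission.

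**Safeguards exist.** The statistician is masked until the main analysis is done, so that person's choice of scale for the primary model would be made blind to arm. Changes will be reported. The independent scrutineers' classifications of adverse events will be reported, non-serious events will be included in safety reporting, and CONSORT items are promised. The change of primary outcomes was approved by the ethics and oversight committees before outcome data were formally examined, so it should not be counted against the trial here. All of this lowers the risk. But masking does not put a transformed estimate back into points, and the text does not say that decisions to omit are taken while masked. Reporting event counts does not commit anyone to the planned between-arm comparison.

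**Stronger readings that the documents do not support.** A reader might infer that bounded scales, with a significant minority near normal physical function at recruitment, make the transformation all but certain. The article relies on diagnostic plots and gives no score distribution. A formal normality test on simulated normal-shaped scores in 5-point steps flagged roughly 34% to 85% of trials, depending on the assumed mean and SD. Under an assumed mixture with a high-scoring minority, the raw scale was flagged almost always but the residuals in only about 5% to 11% of trials. No trigger rate can be stated. A reader might also infer that the rule inflates type I error; step 3 of the check gives no sign of that for a residual-based choice.

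**Conclusion.** The point holds in limited form. If the diagnostics are judged to show a violation, the rule moves the primary regression estimate off the scale on which the trial was sized and is to be interpreted. Under the assumed skewed score, baseline-adjusted regression on raw scores held its level (2.6% against 2.5%), so the transformation is not needed to protect the test. The harm is to interpretability and prespecification. No effect on sample size, power or type I error is shown.

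The omission clause is the weightier half. It leaves primary, CGI and safety comparisons formally open to being dropped. A reader might infer that selective reporting is intended or has occurred; nothing in the article supports that. The defect is that the wording permits it, and disclosing an omission does not supply the missing result.

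The conclusion rests on the wording of the article. The simulation supports only the statement about error rates, and its score distribution is an assumption. An analysis plan that is not shown may already restrict both provisions. The change is worth making but does not undermine the design.

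**What to change.** 1. State that the primary estimate is the baseline-adjusted mean difference in points on the original SF-36 PF and CFQ scales, whatever the diagnostics show.
2. If residuals are non-normal or heteroscedastic, keep the same model and use robust standard errors or a bootstrap confidence interval. Present any transformed analysis only as sensitivity.
3. Drop normality of the scales themselves as a trigger for the regression analyses.
4. Limit the omission clause to exploratory analyses. State that the primary, CGI and safety analyses are always reported as planned, that changes to them are dated before unmasking, and that any post hoc analysis is labelled as such.

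The Results section says that data analysis is under way, so this wording belongs in the analysis plan or a dated protocol note, and the results paper should follow it. The cost is wording only, with no change to sample size, data collection or conduct.

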#### Missing Data

Item-level missing data on the primary and secondary outcome variables at baseline and follow-up will be imputed using mean replacement (prorating). Prorating will be implemented only when less than 20% of item responses per scale are missing. The reasons for missing baseline and follow-up whole-scale data will be summarized using the CONSORT diagram. We will identify baseline characteristics associated with missing data to allow us to impute data to do sensitivity analyses.

#### Analysis for Hypothesis 1

Our primary intention-to-treat analysis will compare the SF-36 PF and CFQ at 12 weeks between groups adjusted using multivariable linear regression analyses [45]. Intention-to-treat (ITT) analyses will be conducted on data from all randomized participants with information at follow-up (ie, modified ITT) regardless of any departure from the allocated treatment arm. We will adjust for our stratification factors (depression, center, and severity of disability) as well as baseline values of outcomes and treatment arm.

A secondary analysis will explore the association between treatment arm and having achieved a clinically useful improvement on the SF-36 PF (ie, an 8-point increase) and the CFQ (ie, a 3-point decrease) using chi-squared analysis.

Analysis of the secondary outcome, the CGI, will compare the proportions scoring “much” or “very much” better (1 and 2), the proportions scoring “a little better,” “no change,” or “a little worse” (3 to 5), and the proportions scoring “much” or “very much” worse (6 and 7) across treatment arms, using an ordinal logistic regression adjusting for our stratification variables.

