### Randomization

The recruiting researcher will log in to the Web-based automated randomization service/system operated by the UK Clinical Research Collaboration (UKCRC) registered King’s Clinical Trials Unit at the Institute of Psychiatry, King’s College London for the intervention allocation, which will be conveyed to the participant by the recruiting researcher. Allocation will be at the level of the individual, using block randomization with randomly varying block sizes, to preserve allocation concealment. Randomization will be stratified by (1) depression (Hospital Anxiety and Depression Scale; cut-off = 11); (2) severity of disability (SF-36 physical functioning subscale ≤40 and ≥45, which was close to the mean score from all participants in the PACE trial [11]; and (3) by center. This will help to ensure equal proportions of depressed and more severely disabled participants in each treatment arm. Automatic emails will confirm the intervention allocation. If for any reason the randomization service is unobtainable, randomization will be completed during the next working day and the participant will be told of the result by telephone.

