#### Primary Outcomes

We initially planned to use the SF-36 PF as the primary outcome analyzed as an interval variable collected at 12-weeks postrandomization. The SF-36 PF is scored as the sum of responses to 10 items related to functioning on everyday activities from getting dressed to performing physical activities, each of which is coded 0 for “Yes, limited a lot,” 5 for “Yes, limited a little” and 10 for “No, not limited at all”. This yields a score ranging from 100 for the highest level of perceived physical functioning to 0 for being unable to bathe or dress oneself. The SF-36 PF was to be the sole primary outcome as we were primarily interested in change in physical function.

However, during recruitment we noticed that a significant minority of participants scored close to the mean of the general population (ie, normal physical function) so could be considered recovered even before any intervention [43]. This is because they had substantial reductions in functioning in other domains, such as mental or social activity levels [7].

We therefore added a second primary outcome, the CFQ, which is scored as the sum of responses to 11 items related to physical and mental fatigue, each of which is coded 0 for less than usual,” 1 for “no more than usual,” 2 for “more than usual” and 3 for “much more than usual,” where usual is how they felt the last time they were feeling well. This gives us a symptomatic measure of fatigue. The two primary outcome variables are valid and reliable and have been used in previous CFS trials [9,11]. The ethics committee, Research and Development (R & D), and the trial steering and data monitoring committees approved this change (in June 2013) before any outcome data were formally examined. Because of the change from one to two primary outcomes, we reanalyzed our power calculation and plan to recruit more participants (see section on sample size).

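### The secondary responder analysis uses an unadjusted chi-square that gives up a little power, and its 8-point SF-36 PF cut is not a value the scale can take

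*Protocol article*

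**What the plan says.** **The responder analysis.** Analysis for Hypothesis 1 introduces it with "A secondary analysis will explore the association between treatment arm" and defines response as "having achieved a clinically useful improvement on the SF-36 PF (ie, an 8-point increase) and the CFQ (ie, a 3-point decrease) using chi-squared analysis". No covariate is named.

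**Its neighbours.** In the same section, the primary linear regressions adjust for depression, center, severity of disability and the baseline value of the outcome. The ordinal logistic model for the CGI adjusts for the stratification variables. Under Randomization, "Randomization will be stratified by (1) depression" is followed by SF-36 PF severity (40 or below against 45 or above) and center.

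**The scales.** Under Primary Outcomes, "The SF-36 PF is scored as the sum of responses to 10 items", "each of which is coded 0 for “Yes, limited a lot,” 5 for “Yes, limited a little” and 10 for “No, not limited at all". The range is given as "This yields a score ranging from 100 for the highest level of perceived physical functioning to 0". The CFQ is "scored as the sum of responses to 11 items related to physical and mental fatigue", each coded 0 to 3.

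**Where the 8 and the 3 come from.** Under Sample Size they are the mean differences assumed for powering the trial: 8 (SD 18) between arms on the SF-36 PF and 3 (SD 6) on the CFQ.

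**Prorating.** Under Missing Data, missing items are mean-replaced when less than 20% of a scale's items are missing.

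**The concern.** Two separate points arise.

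First, the responder test stands between two adjusted analyses and uses none of their covariates. The baseline score is related to who responds, and the stratification factors shaped the allocation. Leaving them out of a binary comparison costs precision and makes this result less comparable with the primary one.

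Second, a between-arm planning difference has become a threshold for individual change, and on the SF-36 PF it lands between two attainable values. A rate of clinically useful improvement is a figure that clinicians and patients are likely to quote. As written, it would be reported as an 8-point gain when every complete-data responder had gained at least 10.

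**Working it through.** **1. The plan's own figures.** With two-sided alpha 2.5% (the article does not state the sidedness) and 80% power, n per arm = 2(z₀.₉₈₇₅ + z₀.₈₀)²(SD/δ)².

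- SF-36 PF: 2 × (2.241 + 0.842)² × (18/8)² ≈ 96.2, so 97; the noncentral t gives 98, as stated. 98/0.9 = 108.9, so 109 per arm and 218 in total, as stated.
- CFQ: 2 × (2.241 + 0.842)² × (6/3)² ≈ 76.0, so 77; the noncentral t gives 78. 78/0.9 = 86.7, so 87 per arm and 174 in total, as stated.

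The 8 and the 3 are therefore the between-arm planning differences, and the sample size is not in question.

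**2. Attainable SF-36 PF changes.** Complete totals are 0, 5, ..., 100, so changes are multiples of 5. None lies from 8 up to, but not including, 10. For complete scores, a gain of at least 8 is the same event as a gain of at least 10.

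**3. Prorated scores.** Less than 20% of 10 items means at most one missing item. A prorated total is 10/9 of a nine-item sum, that is 50k/9 for k = 0 to 18. Any change involving prorated or complete totals is then a multiple of 5/9.

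- 8 ÷ (5/9) = 14.4, so exactly 8 never occurs.
- The values from 8 to below 10 are 15, 16 and 17 times 5/9: 8.33, 8.89 and 9.44.
- Example: baseline 25 (complete), follow-up nine-item sum 30, prorated to 33.33; the change is 8.33. This counts under a cut of 8 and not under a cut of 10.

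**4. CFQ.** Eleven items scored 0 to 3 give totals of 0 to 33 in steps of 1, so a 3-point fall is attainable. The grid problem concerns the SF-36 PF only.

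**5. Chi-square against adjusted tests.** Simulation with 98 per arm, two-sided 5%, 2,000 replicates, and allocation balanced within the 8 strata. Assumed inputs: baseline mean 45, SD 18 at both times, baseline to follow-up correlation 0.6, control gain 3, 35% depressed (4 points lower at follow-up), half at each center (a 2-point difference), and scores rounded to 5 and bounded at 0 and 100.

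| Test | Type I error | Power at an 8-point effect |
|---|---|---|
| Chi-square | 4.1% | 80% |
| Stratified CMH | 5.3% | 82% |
| Logistic, strata and baseline | 5.3% | 85% |

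The Monte Carlo standard error at 5% is √(0.05 × 0.95/2000) = 0.5 points. The 4.1% is therefore about 1.8 standard errors low: mild conservatism, and no sign of inflation.

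**6. Range over assumptions.** Chi-square against baseline-adjusted logistic regression, 98 per arm, 8-point effect, follow-up SD 21, 800 replicates (Monte Carlo standard error about 1.8 points):

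| Baseline SD | Correlation | Chi-square | Logistic | Difference |
|---|---|---|---|---|
| 15 | 0.3 | 54% | 59% | 5 |
| 15 | 0.5 | 65% | 64.5% | nil |
| 20 | 0.5 | 57% | 62% | 5 |
| 25 | 0.5 | 48% | 59% | 11 |

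The only baseline SD in the article is 15, and it belongs to an earlier trial.

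**The case against.** The strongest reply is that this is a secondary, exploratory analysis with no validity problem, and that the primary analysis already adjusts for everything listed. That stands, and it limits the weight of the point. It does not remove it: the chi-square is a stated choice rather than a detail left open, and the adjusted alternative needs no new data.

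It can also be said that the 8-point cut misclassifies nobody with complete data. That is correct. What remains is the label, the few prorated cases, and the use of a group mean difference as an individual threshold without a stated basis.

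Four stronger readings are tempting, but the article does not support them:

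- **That the power loss is about 10 points because baseline scores are widely spread.** The article reports no baseline SD for this trial. It says only that a significant minority scored close to the general-population mean. The loss of about 10 points requires an assumed SD of 25.
- **That baseline imbalance biases the comparison.** Randomization is stratified on SF-36 PF severity, which limits imbalance, and the test allows for the chance imbalance that remains.
- **That many participants cannot respond because of a ceiling.** A 10-point gain is impossible only from an entry score of 95 or 100. With an assumed mean of 45 and SD of 18, about 0.4% enter there, and up to about 3% with SD 25. The actual number is not given. Others near the top have less room, but they can still respond.
- **That a 10-point gain counted as useful conflicts with a 10-point fall counted as serious deterioration.** One is a benefit cut and the other a safety flag, and they can coexist.

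**Conclusion.** The point holds as a modest one on efficiency and labelling. The unadjusted chi-square is valid and slightly conservative (about 4% at a nominal 5%). It typically loses 2 to 5 points of power against a stratified or adjusted test, with a range from nil to about 10. These figures rest on assumed baseline SDs, correlations, control change and covariate effects that the article does not give for this trial.

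That the 8-point SF-36 PF cut operates as at least 10 on complete scores follows from the item coding alone and needs no assumption. It alters no complete-data responder count. It affects how the rate is described and how changes of 8.33, 8.89 and 9.44 are classified. The sample size, the primary analysis and the CFQ cut's attainability are untouched.

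**What to change.** - Replace the chi-square by logistic regression of response on arm, the three stratification factors and the baseline score of the scale analysed. Report the adjusted risk difference with its 95% CI beside the odds ratio.
- State the SF-36 PF cut as a value the scale can take. At least 10 keeps the present classification of every complete score. Say that the 8 and the 3 originate as planning differences, and give the basis for using each as an individual change.
- State how prorated changes between 8 and 10 are classified, and use the operative cut as the label wherever the responder rate is reported.

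The cost is a few sentences and one regression, with no new data and no change to the sample size. The drawback is that the adjusted odds ratio is conditional on the covariates and does not equal the crude one, so the risk difference must accompany it. Under Analysis for Hypotheses 2 and 3 the article already undertakes to report departures from the plan, so the change can be documented there.
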